## Abstract

**Purpose:**

Knee osteoarthritis (KOA) is a common disorder among middle and older individuals. Electroacupuncture and exercise are present as two popular physical therapies for the management of KOA, and both were demonstrated to produce considerable results. However, the clinical decision-making process between these therapeutic interventions remains challenging due to the limited evidence of distinctions in their respective effects. This study aims to evaluate the clinical effect and cost effectiveness of electroacupuncture versus exercise in patients with KOA.

**Study design and methods:**

This is a randomized controlled trial in which 196 symptomatic KOA patients will be randomly assigned 1:1 either to the electroacupuncture group (n = 98) and the exercise group (n = 98). Patients in the electroacupuncture group will receive acupuncture with electric stimulation 3 times a week for 8 weeks, whereas patients in the exercise group will receive neuromuscular training twice a week for 8 weeks. Education concerning KOA management will be provided in both therapies. Co-primary outcomes include changes in numerical rating scale (NRS) and Knee injury and Osteoarthritis Outcome Score (KOOS) Activities of Daily Living (ADL) subscale from baseline at week 8. Secondary outcomes include KOOS Pain subscale, KOOS knee-related Quality of Life (QOL) subscale, Short Form 6 Dimensions (SF-6D), five-level EuroQol five-dimensional questionnaire (EQ-5D-5L), Credibility/ Expectancy Questionnaire, Patient’s global assessment (PGA), 30-second Chair Stand Test (30s-CST), 40m (4*10m) Fast Paced Walk Test (40m FPWT), and Daily Physical Activity level (DPA).

**Discussion:**

The results of this study will provide evidence regarding differences between these 2 physical therapies in multiple aspects and will provide specific guidance for the development of treatments based on the needs of individual patients.

**Trial registration:**

ChiCTR2300070376.

## Introduction

Knee osteoarthritis (KOA) is an important cause of chronic pain and physical dysfunction among middle-aged and elderly populations [1]. Recent years seen a rise in the worldwide prevalence of KOA [2], with a prevalence of symptomatic KOA reached 8.1% in China [3]. For the rapid aging of population, the social burden of KOA will increase further. Although non-steroidal anti-inflammatory drugs (NSAIDs) remain the first-line of treatment, their limited benefits and potential for gastrointestinal bleeding and cardiovascular events were noted [4]. Consequently, nonpharmacologic therapies are receiving increased attention for the management of mild to moderate KOA [5–7].

Intervention for the management of KOA is varied. Exercise showed strong evidence in managing KOA, with multiple forms of exercise delivery proven to be better than non-exercise [8–11]. Acupuncture is another nonpharmacologic therapy which showed favorable evidence. Compared to the sham acupuncture, acupuncture can relieve pain and dysfunction [12–14]. Considering the safety and potential benefits, acupuncture was partly recommended by certain guidelines [6,7,15]. Electroacupuncture is the type of acupuncture recommended for research by National Institute for Health and Clinical Excellence. Its potential better effect was observed in our previous study [13]. Benefits to the convenience and standardization of operation, electroacupuncture is more widely used in clinical practice. In early studies focused on both acupuncture and exercise, acupuncture was designed to be a supplement [16–18]. Considering the cost of time and expenses, it can be difficult for patients to adopt multiple nonpharmacologic therapies. The popularity of acupuncture and exercise varies across different regions. Understanding their respective advantages and characteristics can provide a basis for personalized selection. For lack of attention, evidence regarding the differences between acupuncture and exercise is insufficient. To our knowledge, only one trial compared acupuncture with exercise directly [19]. However, the inclusion of patients in surgery waiting list was limited in generalization. From an economic point of view, both acupuncture and exercise were proved to be cost-effective options for KOA in the developed countries. In a German study compared acupuncture with routine care in treating KOA, the overall Incremental Cost-Effectiveness Ratio (ICER) was 17,845 Euros per Quality-Adjusted Life Year (QALY) gained [20]. In another Denmark study compared supervised exercise with education, the ICER ranged from 6,229 to 20,688 Euros per QALY [21]. However, few studies focused on the difference between the cost-effectiveness of acupuncture and exercise directly. Meanwhile, due to economic and medical resource constraints in developing countries, the cost-effectiveness of acupuncture and exercise may be disparate from that in developed countries. To save conserve resources, it is necessary to find the more cost-effective therapy.

This randomized controlled trial aims to: (1) evaluate the effectiveness of electroacupuncture versus exercise in alleviating pain and improving function in patients with KOA; (2) compare the cost effectiveness of acupuncture and exercise in treating KOA.

## Methods

### Study design

This will be a pragmatic, two-arm, randomized controlled trial conducted in 2 centers in China. A total of 196 KOA patients will be randomly assigned to the electroacupuncture group and the exercise group in a ratio of 1:1. The trial duration will be 24 weeks, comprising 8 weeks of treatment and 16 weeks of follow up. The study protocol has been approved by The Ethics Committee of Dongzhimen Hospital Affiliated to Beijing University of Chinese Medicine (2022DZMEC-165-02) and Peking University People’s Hospital (2021PHB431-001), and registered on Chinese Clinical Trial Registry (ChiCTR2300070376. Date: April 04, 2023. Version 1.0.). This protocol will be reported in accordance with Standard Protocol Items: Recommendations for Interventional Trials (SPIRIT) [22]. Fig 1 illustrates the SPIRIT schedule. S1 File shows the SIPRIT checklist and S2 File shows the original protocol approved by the ethics committee.

**Fig 1 pone.0305105.g001:**
[figure not shown]
SPIRIT schedule. *, primary outcome. Abbreviation: AFT, after the first treatment; KOOS, Knee injury and Osteoarthritis Outcome Score; ADL, Activities of Daily Living; QOL, Quality of Life; SF-6D, Short Form 6 Dimensions; EQ-5D-5L, Five-level EuroQol five-dimensional questionnaire; PGA, Patient’s global assessment; 30s-CST, 30-second Chair Stand Test; 40m FPWT, 40m (4x10m) Fast Paced Walk Test; DPA, Daily Physical Activity level.

### Study site

Recruitment, intervention and follow up will be conducted at Peking University People’s Hospital and Dongzhimen Hospital Affiliated to Beijing University of Chinese Medicine simultaneously. Following randomization, patients will be allotted to the respective group. Recruitment will take place on outpatient departments, with intervention and follow up occurring in dedicated rooms within the hospitals.

### Participants

#### Inclusion criteria

Patients will be eligible if they: (1) aged 45–75, any gender; (2) meet the American College of Rheumatology (ACR) diagnostic criteria [23] of KOA; (3) report knee pain for more than 3 month; (4) had radiological examination within 6 months indicating Ⅱ or Ⅲ in Kellgren–Lawrence (KL) grade [24] with medial more than lateral tibiofemoral osteoarthritis on at least one knee; (5) score 4 or greater in numerical rating scale (NRS) for the past week; (6) are willing to sign the informed consent. Diagnosis and KL classification will be performed by orthopedic surgeons.

#### Exclusion criteria

Patients will be ineligible if meet any of the following points: (1) prior knee surgery on the evaluating knee or pending any surgery for either knee; (2) knee pain due to other pathologies (e.g., meniscus tear, rheumatoid arthritis, joint cavity infection, malignancy, gout, lumbosacral diseases with symptom of lower extremity, etc.); (3) arthroscopy history within 1 year or intraarticular injection history within 6 months for the evaluating knee; (4) either knee having received acupuncture/exercise therapy in the last 6 months; (5) severe acute or chronic organic or neuropsychiatric disorder; (6) disorders of coagulopathy (e.g., hemophilia); (7) pacemakers or epilepsy; (8) pregnancy preparation, pregnant or lactation period; (9) participated in other clinical studies within the past 1 month.

### Allocation

Patients will be randomly assigned to the electroacupuncture group or exercise group in a ratio of 1:1, using block randomization. Random sequences will be programmed by an independent statistician using STATA 17 software. Concealed allocation will be maintained through the use of opaque sealed envelopes containing serial numbers on the outside and a sheet of paper with the random sequence on the inside. Following obtain the written informed consent (S3 File), eligible patients will be asked to complete a general information form including name, gender, age, medical history, etc. as the baseline demographic assessment. Due to the particularity of Daily Physical Activity level (DPA) which cannot be evaluated immediately at the time of recruitment, patients will enter a 1-week preparation period after screening. When the preparation period is finished, the remaining baseline assessments will be measured. After that, a researcher will sequentially open an envelope and allocate the patient to the corresponding center for intervention. The random allocation sequence and the opaque sealed envelopes will be kept separately by a researcher.

### Blinding

Outcome evaluators and statistical analysts will be blinded. Due to the considerable differences between the two therapies, blinding of therapists and patients is not feasible.

### Interventions

For patients with unilateral knee osteoarthritis, treatments will be performed on the affected side which will be defined as the evaluating side. For those with bilateral osteoarthritis, treatments will be performed on both knees, with the more serious side being evaluated. In the event of similar conditions on both sides, flipping a coin to decide which side to evaluate. For both groups, the compliance of the intervention will be recorded. Any other treatment that may affect symptoms during the trial is prohibited, including drug therapy (NSAIDs, opioids, etc.) and physical therapy (tuina, hydrotherapy, etc.). When necessary, patients can receive Diclofenac Sodium Enteric-coated Tablets (Voltaren, Beijing Novartis Pharma Co., Ltd) as the rescue medication, except within 48 hours prior to the evaluation; timing and dosage will be documented meticulously. Education will be accompanied by both interventions, in a form of simulating doctor-patient communication in real treatment environment. This will include information regarding the definition, clinical manifestation, diagnosis, etiology, risk factors, anatomy of the knee joint, treatment, prevention measures and pain manage of KOA, with the aim of helping patients to better understand the condition. In addition, patients with a Body Mass Index (BMI) >25 will be encouraged to lose weight.

#### Electroacupuncture

Patients in the electroacupuncture group will receive treatment 3 times a week, which has been confirmed by our previous study [25] as the better frequency for 8 weeks (a total 24 sessions). An interval of one or two days between each session will be advisable, and repeated session in one day will be prohibited.

A semi-standardized acupoints selection method will be used. The prescription was formulated based on clinical experience and reviews, and is consistent with our previous study [13].

The semi-standardized prescription contains fixed and optional acupoints. *Dubi* (ST35), *Neixiyan* (EX-LE5), *Ququan* (LR8), *Xiyangguan* (GB33) and an *Ashi* point (the point where the patient feels the most pain) are fixed points in this study, which means they will be chosen for all patients. An additional 22 acupoints make up the optional acupoints. The acupuncturist will select three of these optional acupoints based on the meridians corresponding to the pain site. Further details of electroacupuncture are provided in Table 1, with acupoint locations, corresponding needle type and depth of insertion shown in Table 2. Positioning of all acupoints follows World Health Organization’s Standard Acupuncture Locations. The electroacupuncture intervention will be delivered by three acupuncturists from Dongzhimen Hospital Affiliated to Beijing University of Chinese Medicine, each possessing over three years of clinical experience.

**Table 1 pone.0305105.t001:** Details of the electroacupuncture intervention.

Item	Parameter
Needling instrument	length: 25–50 mm, diameter: 0.25 mm; Hwato, Suzhou, China
Retaining time	30min
Treatment sessions	24
Frequency	Three times a week
Manipulation	After the needle inserted, lift, thrust and thrill smoothly for at least 10s to achieve De qi.
Electrical acupoints	Wire 1: LR8 and GB33. Wire 2: 2 of 3 adjunct acupoints.
Electric parameter	Disperse-dense wave. The current will be increased slowly from zero to the degree which the participant can feel but tolerate.

De qi is a multidimensional sensation of numbness, soreness, distention, heaviness during acupuncture stimulation.

**Table 2 pone.0305105.t002:** Acupoints’ locations, corresponding needle type and depth of insertion.

Acupoint	Name	Location	Needle type	Depth of insertion
Fixed acupoints	Dubi (ST35)	On the anterior aspect of the knee, in the depression lateral to the patellar ligament	0.25×40mm	25~40mm
	Neixiyan (EX-LE5)	On the anterior aspect of the knee, in the depression medial to the patellar ligament	0.25×40mm	25~40mm
	Ququan (LR8)	On the medial aspect of the knee, in the depression medial to the tendons of the semitendinosus and the semimembranosus muscles, at the medial end of the popliteal crease	0.25×25mm	20~25mm
	Xiyangguan (GB33)	On the lateral aspect of the knee, in the depression between the biceps femoris tendon and the iliotibial band, posterior and proximal to the lateral epicondyle of the femur	0.25×40mm	25~40mm
	Ashi point	The point where the patient feels most pain	depends on the location	
Optional acupoints for yangming meridian syndrome	Futu (ST32)	On the anterolateral aspect of the thigh, on the line connecting the lateral end of the base of the patella with the anterior superior iliac spine, 6 cun^a^ superior to the base of the patella	0.25×40mm	25~40mm
	Liangqiu (ST34)	On the anterolateral aspect of the thigh, between the vastus lateralis muscle and the lateral border of the rectus femoris tendon, 2 cun superior to the base of the patella	0.25×40mm	25~40mm
	Heding (EX-LE2)	On the anterior aspect of the thigh, in the depression superior to the base of the patella	0.25×25mm	13~20mm
	Zusanli (ST36)	3 cun directly below ST35, and one finger-breadth lateral to the anterior border of the tibia	0.25×50mm	25~50mm
	Fenglong (ST40)	On the anterolateral aspect of the leg, lateral border of the tibialis anterior muscle, 8 cun superior to the prominence of the lateral malleolus	0.25×40mm	25~40mm
Optional acupoints for three-yin meridian syndrome	Xuehai (SP10)	On the anteromedial aspect of the thigh, on the bulge of the vastus medialis muscle, 2 cun superior to the medial end of the base of the patella	0.25×40mm	25~40mm
	Yingu (KI10)	On the posteromedial aspect of the knee, just lateral to the semitendinosus tendon, in the popliteal crease	0.25×40mm	25~40mm
	Yinlingquan (SP9)	On the tibial aspect of the leg, in the depression between the inferior border of the medial condyle of the tibia and the medial border of the tibia	0.25×50mm	25~50mm
	Xiguan (LR7)	On the tibial aspect of the leg, inferior to the medial condyle of the tibia, 1 cun posterior to SP9	0.25×40mm	25~40mm
	Sanyinjiao (SP6)	On the tibial aspect of the leg, posterior to the medial border of the tibia, 3 cun superior to the prominence of the medial malleolus	0.25×40mm	25~40mm
	Taixi (KI3)	On the posteromedial aspect of the ankle, in the depression between the prominence of the medial malleolus and the calcaneal tendon	0.25×25mm	13~25mm
	Taichong (LR3)	In the depression anterior to the junction of the first and second metatarsal bones	0.25×25mm	13~25mm
	Gongsun (SP4)	On the medial aspect of the foot, anteroinferior to the base of the first metatarsal bone, at the border between the red and white flesh	0.25×25mm	13~25mm
Optional acupoints for taiyang meridian syndrome	Weiyang (BL39)	On the posterolateral aspect of the knee, just medial to the biceps femoris tendon in the popliteal crease	0.25×40mm	25~40mm
	Weizhong (BL40)	On the posterior aspect of the knee, at the midpoint of the popliteal crease	0.25×40mm	25~40mm
	Chengshan (BL57)	On the posterior aspect of the leg, at the connecting point of the calcaneal tendon with the two muscle bellies of the gastrocnemius muscle	0.25×50mm	25~50mm
	Kunlun (BL60)	On the posterolateral aspect of the ankle, in the depression between the prominence of the lateral malleolus and the calcaneal tendon	0.25×25mm	13~20mm
Optional acupoints for shaoyang meridian syndrome	Fengshi (GB31)	On the lateral aspect of the thigh, in the depression posterior to the iliotibial band where the tip of the middle finger rests, when standing up with the arms hanging alongside the thigh	0.25×50mm	25~50mm
	Yanglingquan (GB34)	On the fibular aspect of the leg, in the depression anterior and distal to the head of the fibula	0.25×40mm	25~40mm
	Waiqiu (GB36)	On the fibular aspect of the leg, anterior to the fibula, 7 cun proximal to the prominence of the lateral malleolus	0.25×40mm	25~40mm
	Xuanzhong (GB39)	On the fibular aspect of the leg, anterior to the fibula, 3 cun proximal to the prominence of the lateral malleolus	0.25×25mm	13~20mm
	Zulinqi (GB41)	On the dorsum of the foot, distal to the junction of the bases of the fourth and fifth metatarsal bones, in the depression lateral to the fifth extensor digitorum longus tendon	0.25×25mm	8~13mm

^a^ 1 cun (≈20 mm) is defined as the width of the interphalangeal joint of patient’s thumb.

The exercise program will be carried out in groups of 8–10 patients. All exercise interventions will be supervised by 3 licensed therapists from Peking University People’s Hospital, each possessing over three years of clinical experience. More details of the exercise program could be found in S4 File and published protocol [28].

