### Sample size

Based on previous study [13,37], we estimated that the difference in effect size between the 2 groups would be no more than 0.5. Between-group variations in NRS and KOA were expected to be 1 and 8 at week 8, respectively, with the standard deviations (SD) of 2 and 16. With 2-side α = 0.025 (adjusted for two primary outcomes), 77 patients per treatment group are required to test a difference in effect size of 0.5 with 80% power. Taking into account a 20% dropout rate, a total of 196 patients are expected to be recruited.

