### Statistical analysis

SPSS 26.0 software will be used for statistical processing. Measurement data will be expressed as mean and standard deviation, or median and interquartile ranges. Counting data will be expressed as percentages.

All randomly grouped patients with at least 1 session of intervention received will be included in the modified intention-to-treat (mITT) analysis. Multiple imputation will be used to fill the missing data. Five datasets for the missing data will be imputed by the observation value of age, gender, body mass index, KL grade and outcomes from other timepoints. All between-group comparison on repeated measure continuous outcomes (NRS, KOOS ADL, KOOS QOL, SF-6D, EQ-5D-5L, 30s-CST and 40m FPWT, DPA, except PGA) will be assessed by mixed-effect models using outcome scores at all assessed timepoints as the dependent variable, intervention as the main factor, and the baseline value as the covariate. PGA will be assessed by chi-squared test. Sensitivity analysis will be conducted on the primary outcomes (NRS and KOOS ADL) in 2 datasets. First, the dataset without imputation will be analyzed to address potential imputation bias. Second, the per-protocol (PP) set, which will be defined as receiving a minimum of 19 (electroacupuncture) or 12 (exercise) sessions with no obvious protocol violation, will be analyzed to address the compliance. For primary outcomes, *P* < 0.025 will be considered statistically significant (Bonferroni correction). Secondary outcomes will be considered exploratory, and *P* < 0.05 will be considered statistically significant.

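### Exercise is delivered in classes of 8–10, but neither the stated primary model nor the sample size allows for class clustering, so the 0.025 error rate is not protected and 80% power is not assured

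*Protocol article*

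**What the plan says.** Patients are randomised individually, 1:1 (Allocation). On delivery, the Exercise section states: "The exercise program will be carried out in groups of 8–10 patients". Three therapists from one hospital supervise 16 sessions over 8 weeks. The Electroacupuncture section names three acupuncturists, has part of the point prescription chosen for each patient, and describes no group format.

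The Sample size section takes the differences in the two primary outcomes as "expected to be 1 and 8 at week 8, respectively, with the standard deviations (SD) of 2 and 16", and concludes: "With 2-side α = 0.025 (adjusted for two primary outcomes), 77 patients per treatment group are required". The only allowance added is 20% for dropout, giving 196 in total. No ICC or design effect appears.

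The Statistical analysis section specifies mixed-effect models on scores at all timepoints, with "intervention as the main factor, and the baseline value as the covariate". No class or therapist term is named. Each primary outcome is tested at 0.025 after a Bonferroni correction.

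**The concern.** Members of an exercise class share a therapist, a setting and each other's company for up to 16 sessions. If this makes their outcomes alike, the exercise mean is less precise than the same number of independent patients would give. With clustering by class in one arm only, the design is partially nested.

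Two consequences follow, and they belong to different analyses. A model without a class term understates the standard error of the treatment difference. Its confidence interval is then too narrow, and it rejects a true null hypothesis more often than the 0.025 chosen to protect two primary outcomes. A model with a class term can hold the error rate, but it has less power than the independent-patient formula promises, other things being equal.

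**Working it through.** **Inputs.** From Sample size: two-sided α = 0.025, power 80%, differences 1 (SD 2) and 8 (SD 16), both 0.5 SD; 77 per arm; 20% dropout; 196 in total. From Exercise: class size m = 8–10, so about 10–12 classes for 98 patients. Assumed, because the documents do not give it: class ICC 0.01–0.10.

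**The plan's own figure.** With independent patients, n per arm = 2 × ((2.2414 + 0.8416)/0.5)² = 76.04, rounded up to 77. Dividing by 0.8 gives 96.25, so 97 per arm or 194 in total, close to the stated 196. The 77 per arm gives 80.5% power (normal) or 79.8% (t test). The stated figure therefore reproduces, with no allowance for clustering.

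**Formulas with clustering in the exercise arm only.** The calculation treats week 8 as a two-sample comparison in SD units.

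- Design effect: DE = 1 + (m − 1) × ICC.
- True variance of the difference is (1 + DE)/n; an independent-patient test uses 2/n.
- Type I error ignoring classes: 2 × (1 − Φ(2.2414 / √((1 + DE)/2))).
- Power with classes modelled: Φ(0.5 / √((1 + DE)/n) − 2.2414).
- Total N for 80% power: (1 + DE) × ((2.2414 + 0.8416)/0.5)² per arm, divided by 0.8 and doubled, rounding up at each step.

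**Worked case, m = 9, ICC 0.05.** DE = 1 + 8 × 0.05 = 1.40. The standard error ratio is √(2.40/2) = 1.095, and 2.2414/1.095 = 2.046, so the type I error is 0.041. For power, √(2.40/77) = 0.1765 and 0.5/0.1765 = 2.832; Φ(2.832 − 2.241) = 72%. With Satterthwaite degrees of freedom (about 21) it is 66%.

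**Results for m = 8 to 10, 77 per arm, no gain from baseline:**

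| ICC (assumed) | DE | Type I error, classes ignored | Power, classes modelled (normal) | Same, Satterthwaite df | Total N for 80% (normal) |
|---|---|---|---|---|---|
| 0.01 | 1.07–1.09 | 0.028 | 79% | 73–75% | 198–200 |
| 0.02 | 1.14–1.18 | 0.030–0.032 | 77–78% | 71–73% | 206–208 |
| 0.05 | 1.35–1.45 | 0.039–0.043 | 71–73% | 64–68% | 226–236 |
| 0.10 | 1.70–1.90 | 0.054–0.063 | 63–67% | 55–61% | 258–278 |

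The Bonferroni bound over two outcomes is twice the third column: about 0.055–0.125 instead of 0.05.

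**Simulation check.** Forty thousand runs, 10 classes of 8 against 78 individuals, with a t test that ignores classes, gave type I errors of 0.027, 0.031, 0.039 and 0.053 at the four ICCs.

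**Smaller classes.** If 20% dropout shrinks classes of 8 to about 6.4, the type I errors are 0.027, 0.029, 0.035 and 0.047, and the totals for 80% power are 198, 204, 218 and 244.

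**Credit for baseline.** The model fits the baseline value, but the sample size takes no credit for it. If baseline and week-8 scores correlate 0.5 (assumption), the variance is multiplied by 1 − 0.5² = 0.75. Taking the ICC as that of the adjusted outcome, power with classes modelled becomes 90%, 88–89%, 84–86% and 77–80% (normal), or 86–87%, 84–86%, 78–81% and 69–74% (Satterthwaite).

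**The case against.** The strongest reply is that every size above depends on an ICC the documents do not supply. Exercise level is set for each patient, which may keep the ICC small; at 0.01–0.02 the error rate is only about 0.028–0.032. Random-effects structure and degrees of freedom are commonly left to a statistical analysis plan, which is not shown and could contain a class term. This stands as a limit on severity and confidence. It does not remove the point: the sample size, as justified, assumes independent patients, and a later analysis plan cannot change that basis.

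A reader might infer that 80% power is simply not delivered. The documents do not support that. The test that ignores classes keeps about 78–80% power up to ICC 0.05, though at an inflated error rate. The class-adjusted test may recover its loss through the baseline covariate.

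A reader might also infer that 80% is a ceiling because the Sample size section says "the difference in effect size between the 2 groups would be no more than 0.5". The next sentence gives expected differences that are exactly 0.5 SD, so this is loose wording and adds nothing here.

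Three further inferences go beyond the text. One-to-one acupuncture is not stated; there is only no group format described. Fixed classes are not stated either: recruitment from May 2023 to June 2025 implies about 98/25.7 = 3.8 exercise patients a month, so a class of 9 would take about 10 weeks to fill and rolling entry is plausible. Finally, case report forms are not shown, so it cannot be said that class membership goes unrecorded.

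**Conclusion.** The point holds as a should-fix. Group delivery in the exercise arm is stated, the sample size makes no allowance for it, and the named model terms do not include it. Any positive class ICC pushes a test without a class term above 0.025; the direction is certain given such correlation, while the size (0.028–0.063) rests on the assumed ICC range and on stable classes of 8–10. Power is not assured rather than shown to fail: a shortfall is clear only at ICC of about 0.05 or more with little gain from baseline. Under rolling entry, correlation could remain, but 10–12 separate classes would not describe it well and the figures would shift.

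**What to change.** 1. Record each exercise patient's class and supervising therapist, if this is not already captured. Recruitment is described as ongoing, and membership may be hard to reconstruct later.
2. In the primary mixed model, add a random class effect in the exercise arm only, with arm-specific residual variance and Satterthwaite or Kenward-Roger degrees of freedom. Specify this before unblinding.
3. If entry is rolling, prespecify how class membership is defined, for example by calendar period and therapist.
4. Restate power for the planned 196 over an assumed range of ICC and baseline correlation. Leave N unchanged.

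The cost is one case report form field, a few lines of analysis text, a slightly wider confidence interval and a more guarded power statement.
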